### Sample size justification and planned data analysis strategy

Assuming as analysis method a RM-ANOVA with the within-subject variable time (before and after intervention [baseline, week 8]) and the between-group variable group (“add-on Celecoxib” versus “add-on placebo”) with *f* = 0.285 and a significance level of *α* = 0.05, a power of 1—*β* = 0.8 and a correlation between the measurements of *r* = 0.5, we calculated that we would need 38 patients (completers) per group (76 in total) to detect differences between groups (G*Power 3.1.9 was used for sample size calculation (Faul et al. 2007)). As we will perform an ITT analysis (linear mixed model analysis, if normality and variance homogeneity assumptions will be fulfilled), 76 patients is the aspired count of patients with 8-week primary endpoint data. Assuming a drop-out rate of 30%, 109 patients (76/0.7 ≈ 109) will have to be randomized. Based on preliminary data showing that 55% of patients with schizophrenia exhibit an inflammatory profile ([name]’ laboratory), we have calculated that (109/0.55 ≈ 199) should be screened. If the distribution of inflamed/non-inflamed participants does not follow this assumption, more patients will need to be screened to reach the inclusion of 109 patients with an inflamed profile. The intention-to-treat (ITT) population includes all patients with an inflamed profile who received at least one dose of IMP. The per protocol (PP) population will include all participants evaluable for the primary endpoint without major protocol violations. The safety population (SP) consists of all patients who entered the trial and will be used for conducting all safety analyses (in accordance with the ITT population).

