A statistical analysis plan will be developed before any analyses will be performed. For the primary endpoint analysis, a linear mixed model non-restrictively assuming an unstructured covariance matrix will be performed with fixed factors group, time and ‘group x time’ interactions. Analyses will be adjusted for centre, BMI, age and gender as obesity, age and gender may impact cytokine levels. Moreoever, an adjustment of those analyses for PANSS total baseline scores in the case of significant group differences will be performed. Baseline differences will be analyses with independent *t* test or Mann–Whitney *U* test. Continuous secondary endpoints will be analysed using linear mixed models adjusted for centre, age, BMI, gender and, if necessary, for related baseline values and with subsequent parametric post-hoc tests if the requirements for this strategy are met (tested by Kolmogorov–Smirnov tests and Levene’s tests). In cases where the assumptions of normality or variance homogeneity are violated, a monotonic continuous variable transformation will be performed. If this first step is not successful, corresponding non-parametric tests will be used. Additionally, binary logistic regression analysis including a factor variable for centres will be performed. Side-effects, AE and SAE will be analysed with descriptive statistics and likelihood-ratio tests. Demographic information will be shown for each group separately. Dichotomous variables will be analysed with likelihood-ratio tests and continuous variables will be analysed using analyses of variance or respective non-parametric tests. All tests of secondary endpoints will be computed in the ITT and per protocol (PP) populations in an explorative manner on a two-sided significance level of 5%. Outcome data of inflamed patients who participated in the double-blind treatment phase will be compared to the outcome data of the non-inflamed patients (naturalistic control group) in an exploratory manner. An interim analysis is not planned.

The primary economic evaluation (add-on study) will be in the form of a within-trial incremental cost–utility analysis appended with further cost-effectiveness analyses conducted both from a health and social care perspective and from a societal perspective (Drummond et al. 2005). All health economic analyses will be based on the ITT sample with multiple imputation of missing data together with extensive sensitivity and uncertainty analyses.

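### The protocol is inconsistent on whether the primary mixed model depends on distribution checks, so the primary method and effect measure are not clearly fixed in advance

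*Protocol article*

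**What the plan says.** All the relevant text is in the protocol article under Sample size justification and planned data analysis strategy.

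- **Sample-size paragraph.** The sentence begins "As we will perform an ITT analysis (linear mixed model analysis, if normality and variance homogeneity assumptions will be fulfilled" and continues with the primary endpoint: "76 patients is the aspired count of patients with 8-week primary endpoint data". The condition is therefore attached to the primary analysis.
- **Analysis paragraph, primary endpoint.** "For the primary endpoint analysis, a linear mixed model non-restrictively assuming an unstructured covariance matrix will be performed", with group, time and their interaction, adjusted for centre, BMI, age and gender. No condition is repeated.
- **Analysis paragraph, continuous secondary endpoints.** Mixed models with parametric post-hoc tests are used "if the requirements for this strategy are met (tested by Kolmogorov–Smirnov tests and Levene’s tests". This is the only place where the tests are named.
- **Analysis paragraph, fallback.** The next sentences read "In cases where the assumptions of normality or variance homogeneity are violated, a monotonic continuous variable transformation will be performed" and "If this first step is not successful, corresponding non-parametric tests will be used". They name no endpoint, no transformation, no criterion for success and no particular rank test.
- **Timing.** "A statistical analysis plan will be developed before any analyses will be performed".

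**The concern.** Normality and variance homogeneity can be checked only on the trial's own outcome data. If the condition in the sample-size paragraph applies, the primary method is not settled until those data have been examined.

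Each branch estimates something different. The mixed model on raw scores gives a difference in PANSS points, which is how the endpoint is defined under Endpoints and safety measures. A transformed model gives a difference on another scale. A rank test gives no mean difference at all. A simple two-group rank test would also carry no adjustment for centre, BMI, age and gender, and could not use patients without a week-8 score, although the plan promises an ITT analysis.

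Neither branch is forced by the design. A mixed model needs roughly normal residuals rather than normal raw scores, and a comparison of means is robust with about 38 completers per arm.

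**Working it through.** **1. Reading the two paragraphs together.** Three readings are possible.

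| Condition in sample-size paragraph | Fallback in analysis paragraph | Result |
|---|---|---|
| applies to primary | applies to all endpoints | primary method and scale depend on the outcome data |
| applies to primary | secondary endpoints only | no primary analysis is stated if the condition fails |
| does not apply | secondary endpoints only | the sample-size paragraph contradicts the primary-model sentence |

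The text needs correcting under each of them.

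**2. The plan's own figures.** Inputs from the sample-size paragraph are f = 0.285, α = 0.05, r = 0.5, m = 2 measurements and N = 76. For the between-group test, λ = f²·N·m / (1 + (m − 1)r) = 0.081225 × 76 × 2 / 1.5 = 8.23 on 1 and 74 degrees of freedom. Power is 0.808, and 0.798 at N = 74, so 76 reproduces. Then 76 / 0.7 = 108.6, rounded up to 109, also reproduces. The point does not rest on these figures, and the fix does not change them.

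**3. Patients a complete-case rank test would lose.** 109 − 76 = 33, or 30% of those randomized. The mixed model keeps them through their baseline score.

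**4. How often checks would trigger a switch.** The documents do not say how many tests are run, on which quantity or at what level, so these gates are assumptions. The data are exactly normal with 38 per arm, and each test is at 5%.

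- Change scores, with one normality test per arm (Kolmogorov–Smirnov corrected for estimated parameters, i.e. Lilliefors) plus one Levene test. If independent, 1 − 0.95³ = 14.3%. Simulated: about 14%.
- Baseline and week 8, with four Lilliefors tests plus two Levene tests. If independent, 1 − 0.95⁶ = 26.5%. Simulated: 25% to 26%.
- Uncorrected Kolmogorov–Smirnov tests alone: about 0.03%.

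Under assumed skewed outcomes, one corrected normality test per arm plus one Levene test rejects in about 56% of trials (gamma, shape 4) and 84% (gamma, shape 2).

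**5. Type I error.** A two-stage rule was simulated: a t test if the checks pass, otherwise Mann–Whitney, with 6,000 replicates. Rejection rates were 0.052 (normal), 0.049 (gamma 4) and 0.047 (gamma 2). The Monte Carlo standard error is √(0.05 × 0.95 / 6000) = 0.003, so no inflation is visible. The transformation step was not simulated because the plan does not name one.

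**6. Power cost of ranking alone.** d = 2f = 0.57, r = 0.5, 38 per arm, normal data.

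| Comparison | Linear | Rank |
|---|---|---|
| Change score, SD√(2(1 − r)) = SD, d = 0.57 | 69% | 66% |
| Baseline-adjusted, d = 0.57 / √(1 − r²) = 0.66 | 81% | 79% |

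Within each row the loss is 2 to 3 points. Between rows the linear test gains about 12 points, and that comes from baseline adjustment rather than from avoiding ranks. With gamma (shape 4) data and a shift of 0.66, the rank test did better than the t test (86% against 81%).

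**The case against.** The strongest reply is that the analysis paragraph, where the primary analysis is specified, states the mixed model without any condition. The Kolmogorov–Smirnov and Levene tests are named only for secondary endpoints, which are tested exploratively, and the fallback directly follows that sentence. On this view the parenthesis in the sample-size paragraph is loose wording. This stands in part: applying the named tests and the fallback to PANSS total is an inference. But the parenthesis sits in a sentence about primary endpoint data, and the fallback is worded around the same two assumptions without naming an endpoint. The reply shows that two paragraphs must be reconciled; it does not remove the problem.

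A second reply is that the unnamed rank test need not be a simple one, since rank methods with covariates or for repeated measures exist, and that the choice can be left to the analysis plan. The first half stands, so the loss of covariates and of 33 patients is conditional on a simple two-group test. The second half does not. The protocol itself states a data-dependent condition, and an analysis plan that follows it would inherit it.

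A reader might also infer that the rule inflates the false-positive rate, or that moving to ranks costs about 15 points of power (66% against 81%). Neither is supported. The simulated type I error stays near 5%, and the 15-point gap mixes ranking with baseline adjustment. The planned model adjusts for baseline PANSS only if the groups differ significantly at baseline, so 81% is not its default power either.

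**Conclusion.** The point holds in a limited form. The protocol contradicts itself on whether the primary mixed model is conditional. Its only stated alternative would change the effect measure and is not clearly confined to secondary endpoints.

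Under the assumed gates and exactly normal data, a switch would occur in about 14% to 25% of trials, almost never with uncorrected Kolmogorov–Smirnov tests alone, and more often if outcomes are skewed. These rates depend on gates and distributions that the documents do not specify. The harm is a primary method and scale that are not fixed. There is no demonstrated type I error inflation, and ranking itself costs little power. The documents do not support the stronger statement that PANSS total will be pre-tested with Kolmogorov–Smirnov and Levene tests.

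**What to change.** - Delete the condition in the sample-size paragraph.
- State that the linear mixed model on untransformed PANSS total is the primary analysis whatever the distribution checks show, with robust standard errors or arm-specific variances if heterogeneity is a concern.
- Limit transformed and rank-based analyses of the primary endpoint to labelled sensitivity analyses.
- Say whether the fallback in the analysis paragraph applies only to the exploratory secondary endpoints.

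This takes a few sentences in the protocol, carried into the analysis plan. It needs no extra data and leaves 76 and 109 unchanged. When the article was submitted, six participants were enrolled and the analysis plan was still to be written, so the change could be made before any analysis.

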### Endpoints and safety measures

The *primary endpoint* will be change in symptom severity in randomized patients following treatment with add-on Celecoxib compared to control patients following treatment with add-on placebo as assessed by total PANSS score changes from baseline to 8 weeks after treatment initiation. *Secondary endpoints* will include disease severity in the positive, negative, and general psychopathology dimensions assessed using the P-PANSS, N-PANSS and GP-PANSS subscale scores (Kay et al. 1987) after 2 and 6 months compared to baseline. Further, Andreasen Remission criteria (Andreasen et al. 2005) after 2 and 6 months will be compared to baseline. Other measures include level of functioning and quality of life assessed by the Global Assessment of Functioning scale (GAF) score (Endicott et al. 1976) and WHO-Quality of Life assessment (WHOQOL-Group 1998) after 2 and 6 months compared to baseline. Please see Table 1 for more information. Participants of this clinical trial are also invited to participate in accompanying health economic analyses. The cost-effectiveness of the used blood-based algorithm for selecting patients for adjunct anti-inflammatory treatment with Celecoxib will be assessed in a prospective economic evaluation as additional research at the Department of Health Economics, Medical University of Vienna. Costs will be estimated from data on service and other resource uses collected via an adapted German version of the HEQ (Kingslake et al. 2017; Simon and Mayer 2016), at baseline, 2-month follow-up and 6-month follow-up. Outcomes will be assessed in terms of Quality-Adjusted Life Years (QALYs) (Drummond et al. 2005) calculated using a the EuroQoL EQ-5D-5L health-related quality of life instrument (EuroQol 1990) based on the German value set (Ludwig et al. 2018), and in terms of broader wellbeing expressed as Capability-Weighted Life Years (CWLYs) (Simon et al. 2021) based on the Oxford CAPabilities questionnaire-Mental Health (OxCAP-MH) instrument (German version) (Simon et al. 2018, 2013; Laszewska et al. 2019). Finally, patients can opt to participate in accompanying biobanking, where serum samples will be collected and stored for future biological analyses at the LMU Department of Psychiatry and Psychotherapy Biobank.

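### As most naturally read, the primary mixed model does not carry the promised adjustment for centre, BMI, age and gender into the treatment contrast, and baseline PANSS is adjusted for only after a significant baseline test

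*Protocol article*

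**What the plan says.** All but the endpoint definition comes from the article's section on sample size and planned analysis.

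- **Model:** "For the primary endpoint analysis, a linear mixed model non-restrictively assuming an unstructured covariance matrix will be performed with fixed factors group, time", plus the group-by-time interaction. No other interaction is named.
- **Covariates:** "Analyses will be adjusted for centre, BMI, age and gender as obesity, age and gender may impact cytokine levels". The text does not say whether they enter as main effects or also by time, or whether BMI is the baseline value.
- **Time:** the sample size paragraph describes a repeated-measures ANOVA with "within-subject variable time (before and after intervention [baseline, week 8" as its two levels.
- **Endpoint** (section on endpoints and safety measures): "total PANSS score changes from baseline to 8 weeks after treatment initiation".
- **Baseline PANSS as a covariate** is conditional: "an adjustment of those analyses for PANSS total baseline scores in the case of significant group differences will be performed".
- **Planning values:** correlation 0.5 between measurements, 76 completers, 30% drop-out, 109 randomised. The ITT set keeps treated patients who have no week-8 value.

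Randomisation is stratified by centre, and there are two German sites. The article announces a statistical analysis plan, which is not shown.

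**The concern.** Taken together, these statements point to a model in which baseline PANSS is a response, group-by-time is the primary contrast, and the four covariates are main effects. A main effect of a time-constant covariate explains the level of PANSS, not its change, and the primary endpoint is a change. An analysis plan that implemented the list literally would report a treatment effect as adjusted for the randomisation stratum and three patient characteristics. For patients with complete data, that effect would be the plain difference in mean change.

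The strongest available covariate, baseline PANSS, would enter only if a baseline test happened to be significant. Under randomisation that should be rare: about one trial in twenty at a 5% level, which is an assumption because the article gives no level for that test. If baseline PANSS is already a response, adding it as a covariate in the same model is also degenerate, since at baseline it would explain itself.

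**Working it through.** **The plan's own figures.** Inputs: f = 0.285, alpha 0.05, power 0.80, r = 0.5, two groups, m = 2 measurements. The between-factors repeated-measures formula gives noncentrality f²Nm/(1 + (m − 1)r) = 0.0812 × 76 × 2 / 1.5 = 8.23 at N = 76. Power is 0.808, against 0.798 at N = 74, so 76 reproduces. Then 76/0.7 = 108.6, giving 109, and 109/0.55 = 198.2, giving 199. This point changes none of these figures. (The formula that reproduces 76 is the one for the group main effect, not for the interaction; that is a separate matter.)

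**Algebra for complete pairs.** Let G be group and X the covariates.

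- Baseline: Y0 = a + gG + c′X + e0
- Week 8: Y8 = a + t + (g + δ)G + c′X + e8
- Change: D = Y8 − Y0 = t + δG + (e8 − e0)

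The term c′X has cancelled from D. Given D, baseline has mean (a − κt) + (g − κδ)G + c′X + κD. Its intercept, group coefficient, covariate coefficients, slope κ and residual variance are all free under an unstructured covariance. The likelihood therefore splits into a part for D and a part for Y0 given D, with no shared parameters. The estimate of δ comes from regressing D on G alone, so it is the raw difference in mean change.

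**Numerical check.** REML fits, 60 simulated datasets per scenario. From the plan: r = 0.5, 76 completers, and 109 randomised with 33 lacking week 8 (0.30 × 109 = 32.7). Assumed: residual SD 15 and the covariate effects, either equal at both times or larger at week 8.

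*Complete data, n = 76:*

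| | Equal effects | Unequal effects |
|---|---|---|
| Largest shift from main-effect covariates | 6 × 10⁻¹³ | 5 × 10⁻¹³ |
| Mean shift from adding covariate-by-time terms | 0.6 points | 1.5 points |
| Mean SE: none / main effects / by time | 3.358 / 3.358 / 3.453 | 3.838 / 3.838 / 3.506 |

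Main effects leave both the estimate and its SE unchanged. Covariate-by-time terms lower the SE by about 9% (3.506/3.838 = 0.913) when the covariates predict change. When they do not, the SE rises by about 3% (3.453/3.358 = 1.028).

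*109 randomised, 33 without week 8:* patients with baseline only tie the two parts of the likelihood together, so the identity is no longer exact. Across equal and unequal effects, and missingness either completely at random or dependent on observed data, main-effect covariates moved the estimate by 0.34 to 0.48 points on average. The largest shift was 1.0 to 1.8 points, depending on the scenario. The mean SE fell by about 0.5 to 2% (for example 3.303 to 3.286, and 3.831 to 3.746).

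**Gain from always adjusting for baseline.** With equal variances at both times, and relative to the PANSS variance:

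- change score: 2(1 − r) = 2 × 0.5 = 1.00
- week 8 adjusted for baseline: 1 − r² = 1 − 0.25 = 0.75

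That is 25% lower. The ratio is (1 + r)/2, so the gain would be 35% at r = 0.3 and 15% at r = 0.7. If the other covariates explain 0 to 10% of what remains (an assumption), 0.75 becomes 0.75 to 0.675.

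**The case against.** The best reply is that the article does not commit to this model. It never says main effects and does not exclude covariate-by-time terms. Time is defined as baseline and week 8 in the sample size assumption, not in the model sentence. PANSS is also scheduled at the last follow-up visit, and a model of change scores at the two later visits would let main-effect covariates reach the week-8 contrast. Such detail commonly belongs in the analysis plan, which is announced but not shown.

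Much of this stands, and the point is worded as a natural reading for that reason. It does not remove the point. The article names its fixed effects and one interaction only, defines the endpoint as a change, and expressly makes baseline adjustment depend on a test. That last rule is stated, not omitted. Treating BMI as time-varying would not rescue the adjustment, because it would condition on a value measured after randomisation.

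A reader might infer three stronger things, none of which the documents support:

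- **That the planned ITT estimate would be numerically unadjusted.** This is exact only for complete pairs; with the planned drop-out and this ITT set, the covariates do move the estimate somewhat.
- **That the article rules out covariate-by-time terms.** It is silent on them.
- **That the treatment effect would be biased.** Allocation is randomised, so failing to adjust costs precision only.

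It is also fair to say that the gain from BMI, age, gender and centre may be nil. The simulated shifts show the mechanism under assumed covariate effects and do not measure this trial.

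**Conclusion.** The point holds with those limits. On the natural reading, the covariates contribute nothing to the contrast among patients with both PANSS values. With about 30% of week-8 values missing they contribute little, and only through patients who have baseline alone. The complete-pair identity is algebraic and needs only time-constant covariates with one coefficient across both times, and an unstructured covariance. The drop-out figures rest on the assumed SD and covariate effects.

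The consequence is lost precision and an estimate described as adjusted when it largely is not. The most useful loss to recover is that from baseline PANSS: 25% of the variance at r = 0.5 with equal variances, compared with an unadjusted change score. The change is worth making, but it is not a fatal flaw and does not alter the sample size.

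**What to change.** Specify the primary model as week-8 PANSS total on group, baseline PANSS, centre, baseline BMI, age and gender. Baseline PANSS is always included, and the significance test that now triggers its inclusion is dropped.

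If baseline is to stay a response, so that ITT patients without week-8 data remain in the likelihood, constrain the two baseline group means to be equal and add covariate-by-time terms for centre, baseline BMI, age and gender. Do not also enter baseline PANSS as a covariate in that version. In either case, state the form of each covariate and that BMI is the baseline value.

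The cost is wording in the analysis plan, with no new data. In the regression version, baseline PANSS, centre (two sites), BMI, age and gender (taken as two categories) use five degrees of freedom, leaving 76 − 2 − 5 = 69 of the 74 residual degrees of freedom at 76 completers.

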### Study population

Inclusion criteria are defined as follows: (1) In- and outpatients (men and women) aged between 18 and 65 years with a DSM-V diagnosis of schizophrenia or schizophrenia-spectrum disorder confirmed by the Mini-International Neuropsychiatric Interview (Sheehan et al. 1998). (2) Participants are able to give and sign informed consent, (3) must receive a stable antipsychotic treatment for at least one week, (4) must have a total score ≥ 55 on the Positive and Negative Syndrome Scale (PANSS) (Kay et al. 1987), and (5) must display an "inflamed" serum profile (as defined below). (6) Female participants must have a negative pregnancy test (serum) at baseline and must use a method of contraception that is medically approved by the health authority. (7) Previously unknown rheumatological or hepatitis B virus (HBV)/hepatitis C virus (HCV) disease must be excluded by predefined blood screening tests. The *Rheuma-VOR* app will also be used to exclude potential ommon chronic autoimmune rheumatic diseases (Schwarting et al. 2019). The 1-week criterion regarding stable state of antipsychotics (see 2) was chosen based on the usual time used for antipsychotic-switchting from registrational trials and feasibility approaches allowing to include inpatients prior to hospital discharge.

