**Fig. 1 Fig1:**
[figure not shown]
Schematic representation of patient inclusion. Unsupervised classification methods will be used to stratify patients as “inflamed” and “non-inflamed” based on the serum levels of several cytokines. Only patients with an “inflamed profile” will enter the randomized-controlled part of the study and receive either Celecoxib or placebo twice daily

Central randomization will be performed prior to enrolment of the first patient and stratified block wise by study centre at the Münchner-Studien-Zentrum (MSZ). The randomization list will then be forwarded to the pharmacy of the University Hospital Heidelberg (Germany) for labelling and distributing of blinded study medication. Randomization will take place as the patients are assigned the next available patient number in chronological order and receive the corresponding medication kit already containing the correct blinded medication. Safety envelopes for emergency unblinding will be available at both study centres and the integrity of the envelopes will be monitored until study end. To preserve the allocation concealment, the randomization sequence will not be shared with the study personnel (see Table 1 for synopsis of study visits and assessments).

**Table 1 Tab1:** Study flow-chart

Day	Screening^a^ V0	Baseline^a^ V1	V2	V3	V4	V5
	− 21 to − 1	0–1	14	56	120	180
Intervention of medication		Administration from day 1 to day 56			Follow-up	
Informed consent^b^	X					
Inclusion/exclusion criteria	X	X				
MINI interview	X					
Demographic data/medical/psychiatric history	X					
Pre-study medication	X	X				
Physical examination	X	X	X	X	X	X
Study laboratory^c^	X	X	X	X	X	X
Pregnancy test (screening strip)	X					
Pregnancy test serum		X				
Check of inflammation profile^d,f^	X			X		
Randomization		X				
Interaction medication check	X	X	X	X		
PANSS^e^	X	X		X		X
Andreasen remission criteria		X		X		X
GAF		X		X		X
WHOQoL		X		X		X
Assessment blood pressure and heart rate	X	X	X	X	X	X
Assessment of weight and BMI	X	X	X	X	X	X
ECG^c^	X		X	X		
Study medication (re-) dispensing		X	X			
Study medication return			X	X		
Discontinuation check			X	X	X	X
SAE/AE		X	X	X	X	X
Concomitant medication		X	X	X	X	X
Health economics^f^		X		X		X
Biobanking^f^						

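### The binary analysis is written without baseline remission status, although the entry rule admits patients already in remission at V1 and that status is recorded

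*Protocol article*

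**What the plan says.** - **Entry (Study population).** A participant "must have a total score ≥ 55 on the Positive and Negative Syndrome Scale". Neither the inclusion nor the exclusion list sets a minimum on individual items or requires that the patient not be in remission.
- **Schedule (Table 1).** The row "Andreasen remission criteria" is marked at V1, V3 (day 56) and V5 (day 180).
- **Endpoint (Endpoints and safety measures).** Remission is a secondary endpoint whose status "after 2 and 6 months will be compared to baseline". How that comparison is made is not described.
- **Analysis (Sample size justification and planned data analysis strategy).** The primary model is adjusted for baseline PANSS total if the groups differ significantly at baseline. For the secondary endpoints, "Continuous secondary endpoints will be analysed using linear mixed models adjusted for centre, age, BMI, gender and, if necessary, for related baseline values". For binary outcomes the text adds that "binary logistic regression analysis including a factor variable for centres will be performed" and does not name the outcome. Later it says that "Dichotomous variables will be analysed with likelihood-ratio tests".
- **Status.** All secondary tests are exploratory at a two-sided 5% level, and a SAP is to be written before any analysis.

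**The concern.** A patient who meets the remission criteria at V1 and still meets them at V3 has the same binary outcome as one who reached remission during treatment. If V3 or V5 status is regressed on arm and centre, the two are not distinguished.

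Patients in remission at V1 cannot newly remit. They can only keep or lose remission. If celecoxib does not change how often they keep it, they raise the rate in both arms and shrink the difference between them. A probably strong predictor of the outcome is also left out, which costs precision.

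At stake is the readability and sensitivity of one secondary result, though one that readers will find easy to quote.

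**Working it through.** **1. Can a patient in remission enter?** The article gives neither the PANSS item structure nor the remission thresholds. Assume 30 items scored 1 to 7 and a severity rule of at most 3 on each of eight core items.

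- Eight core items at 3 give 8 × 3 = 24. Reaching 55 then needs (55 − 24)/22 = 1.41 on average over the other 22 items.
- Every item at 2 gives 30 × 2 = 60.
- Eight items at 3 and 22 at 2 give 24 + 44 = 68.

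All three patterns satisfy the entry rule and the assumed severity rule. A floor on the total therefore does not exclude remission at V1. The share of such patients, q, cannot be derived from the document.

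**2. The plan's own figures.** No rate or power is stated for remission. The numbers available are 76 patients with 8-week data and 76/0.7 = 108.6, rounded up to 109 randomised. Both were set for the primary endpoint. They serve here only as sample sizes.

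**3. Dilution.** Let p be the remission rate among patients not remitted at V1 and s the share of V1 remitters still remitted. The arm rate is q·s + (1 − q)·p. With q and s equal in both arms, the risk difference shrinks by the factor (1 − q). Assumed values: p = 25% (placebo) and 50% (celecoxib), s = 90%. At q = 0 the odds ratio is (0.50/0.50)/(0.25/0.75) = 3.0.

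| q | Placebo rate | Celecoxib rate | Odds ratio |
|---|---|---|---|
| 10% | 0.09 + 0.225 = 0.315 | 0.09 + 0.45 = 0.540 | 2.55 |
| 20% | 0.18 + 0.20 = 0.380 | 0.18 + 0.40 = 0.580 | 2.25 |
| 30% | 0.27 + 0.175 = 0.445 | 0.27 + 0.35 = 0.620 | 2.03 |

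**4. Power without v with V1 status.** Simulated logistic regressions, two-sided 5% Wald test, same assumed rates, inestimable fits dropped:

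| q | 109 patients with data | 76 patients with data |
|---|---|---|
| 10% | 68 v 72% | about 48 v 52–53% |
| 20% | 57 v 64% | about 43 v 47% |
| 30% | 47 v 55% | about 35 v 41% |

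The plan expects 8-week data on 76 patients, so the right-hand column applies: a gain of about 4 to 6 points.

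**5. What adjustment does not do.** With 109 patients the median adjusted odds ratio was about 2.9, 2.8 and 2.6 for q = 10, 20 and 30%, not 3.0. A main-effect covariate still averages the arm effect over V1 remitters, in whom it was assumed to be nil. This is why a separate report on patients not remitted at V1 is useful.

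**6. Other assumed rates.** With 20% v 40%, s = 1 and 38 per arm, the risk difference goes from 0.20 at q = 0 to 0.18, 0.16 and 0.14, and power from 0.48 to 0.37, 0.29 and 0.23. Restricting to patients not remitted at V1 keeps the difference at 0.20, with power 0.44, 0.40 and 0.35. The direction is the same.

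**7. Sparse data.** The covariate's coefficient is not estimable by ordinary maximum likelihood if no V1 remitter loses remission. With s = 90% and 76 patients that has probability (1 − 0.1q)^76: 0.99^76 = 0.47, 0.98^76 = 0.22 and 0.97^76 = 0.10 for q = 10, 20 and 30%. The fix has to allow for this.

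**The case against.** The strongest reply is that this is a condensed article with a SAP to follow, and the covariates of one exploratory binary endpoint are ordinary SAP content. That would dispose of the point if the article were silent. It is not: it lists covariates model by model, gives baseline values to the mixed models, and mentions only centre for the logistic one. A SAP written from this text could well carry that forward.

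Several limits do stand.

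- A reader might infer that the plan counts patients already in remission as treatment successes. It does not say so. The endpoint is described as a comparison to baseline, which may be meant to deal with them. Only the method is left open.
- A reader might infer that remission is certainly modelled with centre alone. The logistic outcome is not named, including a centre factor does not rule out other terms, and the likelihood-ratio rule could govern remission instead. Neither sentence carries a baseline term, however.
- A reader might infer that chance imbalance in V1 remission would bias the comparison. Under randomisation it neither biases the test nor inflates type I error. Adjustment is a gain in precision.
- V1 remitters can lose remission, so they are not uninformative. Setting persistence equal in both arms builds the dilution into the illustration.
- The thresholds, q and all remission rates are assumptions.

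**Conclusion.** The point holds as a modest weakness in a stated method. The entry rule does not keep out patients in remission at V1, V1 status is recorded, the endpoint is framed relative to baseline, and neither binary analysis as written uses that baseline.

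Under the assumed rates the odds ratio falls from 3.0 to between 2.55 and 2.03 as q goes from 10 to 30%, and adjustment recovers about 4 to 6 points of power at 76 completers. If few patients are in remission at V1, the effect is smaller. The conclusion depends on the assumed item rule, on remission being the intended logistic outcome, and on similar persistence in both arms. The endpoint is secondary and exploratory, and neither the primary analysis nor type I error is touched.

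**What to change.** In the SAP:

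1. Name remission at V3 and at V5 as the outcomes of the logistic regression, and say whether the likelihood-ratio rule also applies to them.
2. Add remission status at V1 as a covariate beside centre. This gives effect to the comparison with baseline that the endpoint section announces.
3. As a supplement, report by arm the proportion newly remitted among patients not in remission at V1.
4. State in advance what is done if few patients are remitted at V1: a penalised (Firth) fit, or baseline PANSS total in place of the binary status.

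The cost is wording only. V1 status and baseline PANSS are already collected, and no visit or patient is added. The supplementary table has a smaller denominator.
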